### Power and sample size calculation

Based on the analysis of longitudinal JHCH clinical data, the within-patient variability for HbA1c is low (standard deviation of 0.6% over a 12-month period). To detect a change in HbA1c of 1% at a significance level of 0.05 with power 0.9, the sample size across the three sites needed is 25. If the within-patient variability at the three sites was double that of JHCH (standard deviation of 1.2%), the required sample size would be 90. Allowing for a loss-to-follow-up of 10%, we would aim to recruit a minimum of 100 patients at baseline. There are currently 330 patients across the three sites, and recruitment will continue throughout the study for newly diagnosed patients, with a potential sample size of approximately 400 at study close. This would allow for a recruitment rate of 33% to ensure that the sample size is met.

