### Statistical analysis

The primary analysis will evaluate the change in glycemic control, measured by HbA1c at the individual level, from the 6-month pre-implementation baseline period to the end of the 18-month implementation period. Data will be modeled at the patient level, with clinic means over time used as the primary summary measure for interpretation.

A linear mixed-effects segmented regression model will be fitted, with fixed effects for time pre-intervention (monthly index), period (0 = per-implementation, 1 = implementation), time post intervention (which is zero during pre-intervention months and increments monthly thereafter), site, and patient-level covariates: age, sex, diabetes duration, Aboriginal and Torres Strait Islander status, and SEIFA quintile. The model will include a random intercept for patients to account for potential repeated measurements, and an autoregressive (AR(1)) correlation structure will be examined to account for within-patient autocorrelation over time. Effects will be expressed as (i) immediate level change and (ii) change in monthly slope, both relative to the counterfactual pre-implementation trends. Robust (sandwich) standard errors were calculated. Distributional and other modelling assumptions will be assessed by inspecting residual plots, with transformations or different distributional families (e.g., proportional odds logistic models) considered. Secondary outcomes with repeated measures will be assessed using a similar model with an appropriate distributional family dependent on the outcome type.

To assess the impact of medical outreach clinics in the MNCLHD prior to the study onset, an additional comparison of the primary outcome will be made from the commencement of medical outreach clinics to the commencement of the implementation period.

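### The stated 90% power is not derived from the segmented mixed model: it suffices for an immediate 1% HbA1c drop, but at 90–100 patients not for the change to month 18 or a gradual effect

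*Protocol article*

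**What the plan says.** All references are to the protocol article.

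- **Power and sample size calculation.** From clinical data at the originating hospital, "the within-patient variability for HbA1c is low (standard deviation of 0.6% over a 12-month period"). For a 1% change, "at a significance level of 0.05 with power 0.9, the sample size across the three sites needed is 25". At double that variability, "the required sample size would be 90". Then: "Allowing for a loss-to-follow-up of 10%, we would aim to recruit a minimum of 100 patients at baseline". There are 330 current patients. No test, number of measurements, pre-period length, trend or autocorrelation enters the calculation.
- **Statistical analysis.** The primary model is a linear mixed segmented regression with a pre-implementation monthly trend, a period term, a post-implementation time term and a random patient intercept; AR(1) correlation is to be examined. "Effects will be expressed as (i) immediate level change and (ii) change in monthly slope, both relative to the counterfactual pre-implementation trends".
- **Primary outcome measures** and **Statistical analysis** both describe the primary question as the change from the 6-month pre-implementation period to the end of the 18-month implementation period.
- **Pediatric diabetes services.** Patients attend clinic three to four times a year in both districts.

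**The concern.** The power statement and the primary model sit in adjacent sections but do not describe the same quantity. A before-after mean change needs only the noise in two averages. The segmented model needs a pre-implementation slope, here estimated from 6 months and about two HbA1c values per patient, and then carries it forward 18 months. The uncertainty of that projection dominates the month-18 effect and is absent from the sample size.

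Neither listed coefficient is the change to month 18. In the model's terms that quantity is level change + 18 × slope change.

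This matters because the programme is phased in. The implementation intervention runs over 18 months, families receive the written principles at their first clinic review, and follow-up is three-monthly. A gradual effect falls mainly on the slope and month-18 contrast, where power is weakest. A non-significant result there would carry a 90% power label that it does not have.

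**Working it through.** **1. The plan's own figures.** Take a before-after mean change with SD of the difference √2 × SD, two-sided α 0.05 (sidedness is not stated) and power 0.9:

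n = 2 × (SD × (1.960 + 1.282) / 1)²

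- SD 0.6: 7.6, so 8. SD 1.2: 30.3, so 31.
- Multiplied by three sites: 22.7, so 23 (stated 25), and 90.8, so 91 (stated 90).

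The stated figures are therefore close to a before-after calculation with a factor for three sites. That factor is inferred, because the article names no test. The loss allowance reproduces: 90 / 0.90 = 100.

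**2. Inputs for the primary model.**

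- From the article: 6 months before and 18 after; visits every 3 or 4 months; SD 0.6 or 1.2; effect 1%; α 0.05.
- Assumed: one HbA1c per visit; visit times evenly staggered across patients; the stated SD is the residual SD per measurement; random-intercept SD 1.2; monthly AR(1) of 0 or 0.8; no missing visits.

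**3. Formula.** Each patient's design matrix X has columns for intercept, month, period, and period × months since start. With V = random-intercept variance + residual covariance, the coefficient covariance is C = (Σ XᵀV⁻¹X)⁻¹. The month-18 contrast is c = (0, 0, 1, 18), with SE = √(cᵀCc). Power = Φ(δ/SE − 1.96) + Φ(−δ/SE − 1.96).

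Example, 100 patients, SD 1.2, three-monthly visits, no autocorrelation: SE 1.064, so δ/SE = 0.94 and power = Φ(−1.02) + Φ(−2.90) = 0.154 + 0.002 = 15.6%.

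**4. Why the SE is large.** Two values 3 months apart give a within-patient slope SE of √2 × 1.2 / (3 × √100) = 0.057 per month. The mixed model also uses between-patient information and reaches 0.050. From the centre of the pre-period (month −3) to month 18 is 21 months, and 21 × 0.0504 = 1.06. The projected trend accounts for nearly all of the SE.

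**5. Power for a 1% month-18 contrast** (three-monthly / four-monthly visits):

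| Patients | SD | AR(1) | SE (% HbA1c) | Power |
|---|---|---|---|---|
| 25 | 0.6 | 0 | 1.07 / 1.21 | 15.5% / 13.1% |
| 90 | 1.2 | 0 | 1.12 / 1.28 | 14.5% / 12.3% |
| 100 | 1.2 | 0 | 1.06 / 1.21 | 15.6% / 13.1% |
| 90 | 1.2 | 0.8 | 0.84 / 0.99 | 22.2% / 17.2% |
| 100 | 1.2 | 0.8 | 0.80 / 0.94 | 24.2% / 18.6% |
| 90 | 0.6 | 0 | 0.56 / 0.64 | 42.8% / 34.6% |
| 100 | 0.6 | 0 | 0.53 / 0.61 | 46.6% / 37.7% |
| 90 | 0.6 | 0.8 | 0.42 / 0.50 | 66.3% / 52.3% |
| 100 | 0.6 | 0.8 | 0.40 / 0.47 | 70.9% / 56.6% |
| 330 | 1.2 | 0 | 0.59 / 0.67 | 40.0% / 32.2% |
| 330 | 0.6 | 0 | 0.29 / 0.33 | 92.6% / 84.9% |

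Placing visits differently within the month moves most of these by one to three points.

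**6. The two listed effects**, no autocorrelation.

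- Immediate level change of 1%: with 90 patients at SD 1.2, SE 0.21–0.24 and power 98.5–99.7%. With 25 patients at SD 0.6, SE 0.20–0.23 and power about 99% or more.
- Slope change reaching 1% by month 18 (1/18 = 0.056 per month): with 90–100 patients at SD 1.2, SE 0.051–0.061 and power 15–19%.

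**The case against.** The strongest reply is that the level change is one of the two effects the plan names, and for it the study has ample power. This stands. A reader might infer that the segmented analysis as a whole has only 12–16% power. The article does not support that: the figure belongs to the month-18 contrast at the pessimistic SD without autocorrelation.

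Second, that contrast is never written down, and the reference to the end of the 18 months could describe only the data window. That reading is possible. But both sections present it as the change being evaluated, and on the other reading it is still unstated which effect the 1% belongs to.

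Third, the low figures pair the doubled SD with the minimum recruitment. SD 0.6 is the only value based on data, and 100 is a floor out of 330. This is fair, and the table shows how far it helps: most of the 330 patients at SD 0.6 come near or pass 90%. No scenario with 90–100 patients does.

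Fourth, a reader might infer that 25 and 90 are miscalculated. That is not established. No test is named, a three-site factor gives 23 and 91, and the figures exceed what a pooled before-after comparison needs.

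Finally, detail may lie in a fuller protocol or analysis plan. But the article prints both the power claim and the model, and the mismatch is visible between them.

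**Conclusion.** The concern holds in a limited form. The 90% power is not derived from the declared primary model and is not tied to any of its effects. It is adequate for an abrupt 1% level change. It is not adequate, at the stated minimum of 100 or the 90 remaining after loss, for a month-18 change or for a slope building to 1%. Month-18 power there runs from about 12% to about 71% over the SDs, visit intervals and autocorrelations tried.

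The size rests on the assumptions listed in the working, chiefly one HbA1c per visit and the stated SD acting as the residual SD. The direction is more robust, because it comes from projecting a 6-month trend over 18 months. The result does not show that the study is too small: the outcome depends on how many of the 330 patients are recruited and on the true residual SD.

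**What to change.** In **Statistical analysis**, name one primary contrast: fitted minus counterfactual mean HbA1c at month 18 (level change + 18 × slope change). Keep level change and slope change as supporting estimates.

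In **Power and sample size calculation**, replace the 25 and 90 statements with the power or expected 95% confidence interval half-width of that contrast, at 100 and 330 patients, for SD 0.6 and 1.2 and a range of autocorrelation, with the visit frequency stated. Under the assumptions above and no autocorrelation, the half-width (1.96 × SE) is about 2.1–2.4% HbA1c for 100 patients at SD 1.2, and about 0.6–0.7% for 330 patients at SD 0.6.

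The cost is rewording two sections. No extra patients are needed. The drawback is a less favourable stated power.

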### Statistical analysis

The primary analysis will evaluate the change in glycemic control, measured by HbA1c at the individual level, from the 6-month pre-implementation baseline period to the end of the 18-month implementation period. Data will be modeled at the patient level, with clinic means over time used as the primary summary measure for interpretation.

A linear mixed-effects segmented regression model will be fitted, with fixed effects for time pre-intervention (monthly index), period (0 = per-implementation, 1 = implementation), time post intervention (which is zero during pre-intervention months and increments monthly thereafter), site, and patient-level covariates: age, sex, diabetes duration, Aboriginal and Torres Strait Islander status, and SEIFA quintile. The model will include a random intercept for patients to account for potential repeated measurements, and an autoregressive (AR(1)) correlation structure will be examined to account for within-patient autocorrelation over time. Effects will be expressed as (i) immediate level change and (ii) change in monthly slope, both relative to the counterfactual pre-implementation trends. Robust (sandwich) standard errors were calculated. Distributional and other modelling assumptions will be assessed by inspecting residual plots, with transformations or different distributional families (e.g., proportional odds logistic models) considered. Secondary outcomes with repeated measures will be assessed using a similar model with an appropriate distributional family dependent on the outcome type.

To assess the impact of medical outreach clinics in the MNCLHD prior to the study onset, an additional comparison of the primary outcome will be made from the commencement of medical outreach clinics to the commencement of the implementation period.

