## Methods

### Study design and setting

A pre-post implementation study will be conducted at three sites providing outpatient and inpatient pediatric diabetes care in New South Wales (NSW), Australia. Two of the sites (Port Macquarie and Coffs Harbour) are level 5 public hospitals in the Mid-North Coast Local Health District (MNCLHD). The third center (Nepean) was a level 6 tertiary public hospital in the metropolitan Nepean Blue Mountains Local Health District (NBMLHD). The characteristics of the health districts in comparison to the JHCH, where SWIIM was developed, are presented in **Supplementary Table 2**. The sites were selected to allow analysis of SWIIM implementation in a variety of settings with differing staffing levels and diabetes-specific expertise across metropolitan and non-metropolitan populations.

The implementation of a practice change intervention will occur over an 18-month period (**Supplementary F****igure 1**), during which eligible patients will be recruited. The intervention will be delivered simultaneously across the three sites. Given that the intervention occurs at a site-wide level, a within-center randomization protocol would not be possible. Pre-intervention (usual care) data will be retrospectively obtained from the electronic medical records of recruited the patients. Patients who are newly diagnosed during the study period or for whom retrospective data are not available will also be included for statistical analysis at the available time points (see *Statistical analysis*).

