### Participants and recruitment

#### Pediatric diabetes services

In the MNCLHD, where there are 110 young people with type 1 diabetes, the average HbA1c level is 8.6%. Each of the two sites is served by a general pediatrician, diabetes educator, and dietitian. The diabetes educator and dietitian were also shared with adult diabetes services. The inpatient ward at each site is a mixed pediatric unit staffed by pediatric trained nurses, and there is access to social workers and Aboriginal health officers that service the entire hospital. Pediatric endocrinologists from JHCH provide six monthly outreach clinics to MNCLHD, an arrangement that began 24 months prior to the study commencement. Patients are reviewed in outpatient clinics three to four times per year.

In NBMLHD, where there are 220 young people with T1D, the average HbA1c level is 8.1%. The team comprises pediatric endocrinologists, dietitians, diabetes educators, and social workers. Patients are reviewed in outpatient clinics three to four times per year. The inpatient ward is a mixed pediatric unit staffed by pediatric trained nurses and there is access to Aboriginal health officers.

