#### Primary outcome measures

The primary outcome was glycemic control, measured as HbA1c (%) for each patient, obtained from the EMR. Analyses will be conducted on individual-level data, with modelled effects expressed as changes in the monthly clinic mean HbA1c from the 6-month pre-implementation period to the end of the 18-month implementation period (**Supplementary F****igure 1**). Additional primary outcome data from MNCLHD sites will be collected for the 12 months prior to the commencement of JHCH pediatric endocrinologist outreach clinics through to the commencement of implementation.

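### The segmented model switches its step on fully in the first implementation month, so the lag in HbA1c shrinks the reported level change and creates a slope even when the true effect is immediate and flat

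*Protocol article*

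**What the plan says.** The Primary outcome measures section of the protocol article fixes the endpoint: "The primary outcome was glycemic control, measured as HbA1c (%) for each patient, obtained from the EMR". Effects are to be given on the clinic scale, with "modelled effects expressed as changes in the monthly clinic mean HbA1c".

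The Statistical analysis section sets the comparison "from the 6-month pre-implementation baseline period to the end of the 18-month implementation period" and lists the time terms of a linear mixed segmented regression. One is a monthly pre-intervention index. One is a step, "period (0 = per-implementation, 1 = implementation" (read here as pre-implementation for the zero level). The third is "time post intervention (which is zero during pre-intervention months and increments monthly thereafter". Two effects are reported: "Effects will be expressed as (i) immediate level change and (ii) change in monthly slope, both relative to the counterfactual pre-implementation trends".

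No lag, wash-in or transition term appears. Under Study design and setting, "The intervention will be delivered simultaneously across the three sites". Under Pediatric diabetes services, "Patients are reviewed in outpatient clinics three to four times per year". The Written resources item of the Intervention section gives existing families the summary of SWIIM principles at their first clinic review during implementation.

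**The concern.** A step that goes from 0 to 1 in the first implementation month is right only if the outcome can show the whole effect at once. HbA1c cannot do that, because a value drawn early in implementation still reflects partly the months before. The true curve in HbA1c is therefore a short ramp followed by a plateau. A step and one straight line cannot follow that shape, so least squares makes the step too small and tilts the line downward.

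Both declared effects are then biased. The step understates the benefit. The slope says HbA1c is still improving each month when the effect is already complete, and carrying it to month 18 overstates the end-of-study difference. A conclusion that the benefit keeps growing could come from the assay alone. The AR(1) structure and sandwich errors concern variance. The residual checks lead, as written, to transformations or other distributional families. None of these changes the time structure of the mean.

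**Working it through.** The plan gives no figure for this point to reproduce, and its sample-size figures do not bear on it.

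**Inputs.** From the protocol article: 6 months before and 18 months after the start, the step and clock coding above, and a 1% HbA1c change (Power and sample size calculation) as the illustrative effect. Assumed: flat pre-trend, equal weight per month, values at mid-month (t = -5.5 to -0.5 and 0.5 to 17.5), and a linear marker ramp of L = 2, 3 or 4 months.

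**Model.** Mean = b0 + b1·t + level·period + slope·time-post. Simulated response after the start = -min(t/L, 1), without noise. Effect at month 18 = level + 18·slope. With these terms the pre and post segments are each fitted by their own line.

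**Worked case, L = 3.** The first three post values are -1/6, -1/2 and -5/6, then -1 fifteen times.
- Mean = -16.5/18 = -0.917, at mean time 9.
- Sum of squares of time = 18 × 323/12 = 484.5.
- Cross-product = (-8.5)(5/6) + (-7.5)(1/2) + (-6.5)(1/6) = -11.917.
- Slope = -11.917/484.5 = -0.0246.
- Level = -0.917 + 9 × 0.0246 = -0.695.
- Month 18 = -0.695 - 18 × 0.0246 = -1.138.

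| Assumed ramp | Level | Slope per month | Month 18 |
|---|---|---|---|
| none | -1.00 | 0 | -1.00 |
| 2 months | -0.79 | -0.017 | -1.10 |
| 3 months | -0.70 | -0.025 | -1.14 |
| 4 months | -0.61 | -0.031 | -1.17 |

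Other averaging shapes (uniform, declining and exponential weights) give a step of 62 to 80% of the true one, in the same direction every time.

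**Adding phased first contact.** Three to four visits a year means one every 12/4 = 3 to 12/3 = 4 months. Spreading first exposure evenly over 3 or 4 months on top of the 2- to 4-month ramp gives a level of -0.51 to -0.28 and a month-18 effect of -1.21 to -1.27. The spread of visits alone, with no assay lag, gives a level of -0.70 (3 months) or -0.61 (4 months), the same size as a marker ramp of that length.

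**Leaving out the first 3 implementation months, clock still at month 0.**
- Assay lag only: level -0.96 to -1.00, slope 0 to -0.003.
- With phased contact: level -0.62 to -0.93. A 6-month transition gives -0.96 to -1.00.

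**Precision.** Independent, equal-variance monthly means, in residual SDs. The variance of a fitted line at time x is 1/n + (x - mean time)²/Sxx. Pre segment: n = 6, mean -3, Sxx = 17.5.
- Level, as planned: √[(1/6 + 9/17.5) + (1/18 + 81/484.5)] = 0.95.
- Level, 3 months out, clock at 0 (n = 15, mean 10.5, Sxx = 280): √[(1/6 + 9/17.5) + (1/15 + 110.25/280)] = 1.07, or +12%.
- Level term restarted at month 3: √[(1/6 + 36/17.5) + (1/15 + 56.25/280)] = 1.58, or +66%.
- Slope: √(1/17.5 + 1/484.5) = 0.243 becomes √(1/17.5 + 1/280) = 0.246, or about +1%.
- Month 18: √[(1/6 + 441/17.5) + (1/18 + 81/484.5)] = 5.06 stays 5.06 (rise under 0.1%).
- Level, 6 months out (n = 12, mean 12, Sxx = 143): √[(1/6 + 9/17.5) + (1/12 + 144/143)] = 1.33, or +40%.

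**The case against.** The strongest reply is that an effect complete on day one is not what this study expects. SWIIM is embedded over 18 months and existing families meet it at clinic reviews, so a gradual fall carried by the slope may be real. With uptake ramped over an assumed 6 months and no assay lag, the model already gives a step of -0.44 and a last-month effect of -1.20. A 2- to 4-month uniform HbA1c average moves the latter only to -1.24 to -1.25. With 12-month uptake the lag slightly reduces the overshoot (-1.19 becomes -1.14 to -1.18). This stands: the 10 to 17% illustrates the lag alone and does not forecast this trial's error. It also follows that a reader may not call any negative slope spurious.

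The average change over the whole post period is not distorted by the model form: for L = 3, -0.695 - 9 × 0.0246 = -0.917, the mean of the simulated values. That also stands, but the plan does not name that average as one of its two reported effects.

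A third reply is that a transition term may sit in an analysis plan not shown here. That does not dispose of the point, because the article itself lists the time terms and names the two effects. The point concerns that stated choice.

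**Conclusion.** The point holds as a bias in two named effects. With a 2- to 4-month marker ramp and full exposure at month 0, an immediate and flat 1.0% fall is reported with a step 21 to 39% too small, a slope of -0.017 to -0.031% per month that does not exist, and a month-18 effect 10 to 17% too large. Phased contact makes the step smaller still, and the lag is then one contributor among others. The direction held for every averaging window tried under full exposure at month 0. The size rests on the window, which the documents do not give.

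Two stronger readings are not supported. A reader might infer that the level change is the primary effect. The plan reports it alongside the slope change and defines the primary comparison up to the end of the 18 months. A reader might also infer that HbA1c cannot show a level change at all. The fitted step keeps 61 to 79% of the effect in these scenarios, which is attenuation and not loss.

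**What to change.** In the primary segmented model, prespecify a transition period: exclude HbA1c values from the first 3 calendar months of implementation, or give them their own term. Keep the post-intervention clock at month 0. Relabel effect (i) as a level change after a transition period, and note that with this clock the coefficient is the post-transition line read back to the start of implementation. Report the model-based difference from the counterfactual at one fixed late month. Run 2-, 4- and 6-month transitions as sensitivity analyses, the 6-month one to cover staggered first contact.

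Only analysis wording changes. The standard error rises by about 12% for the level change, about 1% for the slope, and under 0.1% at month 18. The late-month contrast is imprecise in any case (5.06 against 0.95 residual SDs for the level), because it projects a 6-month pre-trend. The 6-month sensitivity analysis costs about 40% on the level. Restarting the level term at month 3 would cost about 66%, and should be avoided or disclosed. A 3-month transition removes nearly all of the assay-driven bias but does not fully absorb slower uptake, and the report should say so.

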**Methods:**

A pre–post-implementation study will be conducted in three hospitals: two non-metropolitan sites in the Mid-North Coast Local Health District (MNCLHD) and one metropolitan site in the Nepean Blue Mountains Local Health District (NBMLHD). An education program will be delivered to clinicians with written resources and clinical support. All children and young people aged 0–18 years with T1D receiving care at these sites receive SWIIM for diabetes management. Data will be collected over an 18-month implementation period with retrospective pre-intervention data for comparison. The primary outcome was the change in HbA1c levels over the implementation period. Secondary outcomes included continuous glucose monitoring (CGM) metrics, insulin therapy modality, adherence to complication screening, hospitalization rates, and program feasibility indicators. Acceptability will be assessed using validated patient- and clinician-reported measures. A cost-effectiveness analysis will be performed to determine the financial impact of implementing the SWIIM over standard care.

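### The primary outcome is one change from baseline to month 18, but the analysis reports a level change and a slope change; neither equals it and neither is named as decisive

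*Protocol article*

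**What the plan says.** Three places describe a single quantity.

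- Abstract, Methods: "The primary outcome was the change in HbA1c levels over the implementation period".
- Primary outcome measures: "modelled effects expressed as changes in the monthly clinic mean HbA1c from the 6-month pre-implementation period to the end of the 18-month implementation period".
- Statistical analysis, first paragraph: the primary analysis concerns the change "from the 6-month pre-implementation baseline period to the end of the 18-month implementation period", with "clinic means over time used as the primary summary measure for interpretation".

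Power and sample size calculation also assumes one effect: "To detect a change in HbA1c of 1% at a significance level of 0.05 with power 0.9". It gives 25 patients at a within-patient SD of 0.6%, 90 at 1.2%, and a recruitment minimum of 100.

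The second paragraph of Statistical analysis specifies a segmented mixed model with a pre-implementation trend, a period indicator and a post-implementation time term. It then states: "Effects will be expressed as (i) immediate level change and (ii) change in monthly slope, both relative to the counterfactual pre-implementation trends". The article gives no contrast at month 18, no rule for combining the two coefficients, and no statement of which one the 0.05 level applies to.

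**The concern.** A reader who follows the plan as written obtains two estimates and no test of the quantity that the plan calls primary. There are three consequences.

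- The decisive coefficient could be chosen after the results are seen.
- The two coefficients can differ in sign, and no conclusion is laid down for that case.
- The sample size is tied to one 1% change without saying which of several quantities, with very different precision, that 1% refers to.

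The study has no concurrent control group and its Discussion already asks for caution about causation, so an open choice of primary effect weakens it further.

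**Working it through.** **Inputs from the protocol article.** Pre-period 6 months, implementation 18 months, change of interest 1%, alpha 0.05, within-patient SD 0.6 or 1.2, 90 patients in the second scenario, 330 current patients, clinic review three to four times a year.

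**Assumptions, not in the article.** Two-sided test; pre-trend index running through all 24 months; random intercept with between-patient SD 1.2; visits every 3 to 4 months; independent residuals; no covariates.

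**Step 1: the plan's own figures.** 90 / (1 - 0.10) = 100 reproduces. The 25 and 90 do not follow from a simple paired calculation: (0.6 x 3.242 / 1)^2 = 3.8, so 4, and (1.2 x 3.242 / 1)^2 = 15.1, so 16. Taking the SD of a difference as sqrt(2) x SD gives 8 and 31. That is a separate matter. Here it is enough that the section speaks of one change and mentions neither a slope nor a counterfactual.

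**Step 2: what the model terms mean.** Write b for the pre-trend per month, L for the level change and S for the slope change.

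- Difference from the counterfactual at month 18 = L + 18S.
- Change from the middle of the baseline (month 3.5 of 24) to the end = 20.5b + L + 18S.

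| b | L | S | L + 18S | Baseline to end |
|---|---|---|---|---|
| 0 | 0 | -0.0556 | -1.0 | -1.0 |
| 0 | -1 | +0.0556 | 0 | 0 |
| -0.05 | 0 | 0 | 0 | 20.5 x (-0.05) = -1.03 |

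Row 1 has the full effect with no level change. Row 2 has two non-zero coefficients and no effect at month 18. In row 3 the defined outcome falls by about 1% while both reported effects are zero.

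**Step 3: precision.** Standard errors come from the generalized least squares covariance of the segmented model. Power for 1% is approximately Phi(1/SE - 1.96). With 90 patients, SD 1.2 and a 6-month baseline:

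| Contrast | SE | Power for 1% |
|---|---|---|
| Level change L | 0.20-0.24 | about 99% |
| Baseline-to-end change | 0.13-0.15 | about 100% |
| L + 18S | 1.1-1.3 | 12-15% |

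For example, 1/1.107 - 1.96 = -1.06 gives about 0.145, and 1/1.3 - 1.96 = -1.19 gives about 0.12.

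Power for L + 18S in other scenarios with a 6-month baseline:

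| Patients, SD | Visits spread over 3-4 months | Visits exactly every 3 months |
|---|---|---|
| 90, 0.6 | 36-40% | 44% |
| 330, 1.2 | 33-35% | 41% |
| 330, 0.6 | 85-88% | 93% |

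**Step 4: a 12-month baseline.** With 90 patients and SD 1.2, the SE of L + 18S falls to about 0.5. Then 1/0.5 - 1.96 = 0.04, which is power of about 50%. It is about 97 to 98% with 90 patients at SD 0.6, or with 330 at SD 1.2.

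**Step 5: two tests.** The estimates of L and S correlate at about 0.6 to 0.7. If success meant either one significant at 0.05, the false-positive rate would be about 8.5 to 9%, against 1 - 0.95^2 = 9.75% if they were independent.

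**The case against.** Reporting level and slope is ordinary practice for segmented regression. The model is not wrong, because every contrast above is a linear combination of its terms. The slope term is there to capture gradual uptake. This is also a condensed article, and decision rules are commonly left to an analysis plan that is not shown. All of that stands. It does not remove the mismatch, which lies between sentences of the article itself: the outcome is fixed as one quantity and the effects are fixed as two others.

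A reader might go further and infer two things that the document does not support.

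- **That the outcome the protocol calls primary is very imprecise.** Read plainly, that outcome is the baseline-to-end change, which is estimated well. The low power belongs to the month-18 difference from the counterfactual, which only the counterfactual wording in Statistical analysis leads to. Even there it depends on the scenario, and 90 patients at SD 1.2 is the pessimistic one.
- **That the false-positive rate is inflated to 8.5 to 9%.** That holds only under an either-coefficient rule, which the protocol does not state.

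**Conclusion.** The point holds as an internal contradiction about the primary effect. The article defines and sizes for one change, then reports two coefficients that do not equal it, and names neither as primary. In the 90-patient, SD 1.2 scenario, power for 1% runs from about 12% to about 100% according to which quantity is taken as primary. The contrast that removes the pre-existing trend is the weak one, because it extrapolates a 6-month trend over 18 months. The contradiction and the worked examples need no assumption beyond the usual reading of the model terms. The power and correlation figures rest on the assumed visit spacing, between-patient SD and error structure. The article says an AR(1) structure will be examined, which would change them. They show that the choice matters and are not a forecast.

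**What to change.** 1. Name one primary contrast in the Abstract, in Primary outcome measures and in Statistical analysis, with one 95% confidence interval and one two-sided 5% test. The preferred choice is the model-based difference from the counterfactual at month 18, L + 18S, because Statistical analysis already measures effects against the counterfactual.
2. Make the level and slope changes supportive, and report the modelled baseline-to-end change beside the primary contrast.
3. Use at least 12 months of retrospective HbA1c from the medical records at all sites in the primary model. The plan already looks back 12 months for screening and hospitalizations, and further for HbA1c at the Mid-North Coast sites.
4. Restate the power for the contrast chosen. A 12-month baseline alone leaves about 50% with 90 patients at SD 1.2, so the recruitment target needs to be looked at again under that scenario.

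The cost is rewording and a longer record extraction, with no added visits. The model would rely on a linear trend over a longer window. At the Mid-North Coast sites a baseline approaching 24 months would reach the start of the outreach clinics, which is itself a change in service.
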